# A non-randomized controlled stepped wedge trial to evaluate the effectiveness of a multi-level mammography intervention in improving appointment adherence in underserved women

**DOI:** 10.1186/s13012-015-0334-x

**Published:** 2015-10-14

**Keywords:** Breast cancer screening, Underserved women, Evidence-based interventions, Patient navigation, Mammogram adherence, Non-randomized controlled trial, Budget impact analysis

## Abstract

**Background:**

Considerable racial and socio-economic disparities exist in breast cancer. In spite of the existence of numerous evidence-based interventions (EBIs) aimed at reducing breast cancer screening barriers among the underserved, there is a lack of uptake or sub-optimal uptake of EBIs in community and clinical settings. This study evaluates a theoretically based, systematically designed implementation strategy to support adoption and implementation of a patient navigation-based intervention, called Peace of Mind Program (PMP), aimed at improving breast cancer screening among underserved women.

**Methods/design:**

The PMP will be offered to federally qualified health centers and charity clinics in the Greater Houston area using a non-randomized stepped wedge design. Due to practical constraints of implementing and adopting in the real-world, randomization of start times and blinding will not be used. Any potential confounding or bias will be controlled in the analysis. Outcomes such as appointment adherence, patient referral to diagnostics, time to diagnostic referral, patient referral to treatment, time to treatment referral, and budget impact of the intervention will be assessed. Assessment of constructs from the consolidated framework for implementation research (CFIR) will be assessed during implementation and at the end of the study (sustainment) from each participating clinic. Data will be analyzed using descriptive statistics (chi-square tests) and generalized estimating equations (GEE).

**Discussion:**

While parallel group randomized controlled trials (RCT) are considered the gold standard for evaluating EBI efficacy, withholding an effective EBI in practice can be both unethical and/or impractical. The stepped wedge design addresses this issue by enabling all clinics to eventually receive the EBI during the study and allowing each clinic to serve as its own control, while maintaining strong internal validity. We expect that the PMP will prove to be a feasible and successful strategy for reducing appointment no-shows in underserved women.

**Trial registration:**

Clinical trials registration number: NCT02296177

**Electronic supplementary material:**

The online version of this article (doi:10.1186/s13012-015-0334-x) contains supplementary material, which is available to authorized users.

## Background

### Importance of mammography adherence in underserved women

Breast cancer is the most common cancer and the second leading cause of cancer mortality among women in the USA [1], with roughly one in eight women developing breast cancer during their lifetime [2, 3]. Substantial breast cancer-related morbidity and mortality disparities persist among the underserved, particularly among African American women [1–6]. Disparities in breast cancer outcomes are due to lower mammography screening rates, lack of timely follow-up of abnormal results, and lack of timely treatment initiation among women with breast cancer. Stage at diagnosis is an important predictor of survival [7, 8]. Women who are diagnosed at a late stage are at higher risk for mortality from breast cancer, and are at risk for complications and overall poorer health outcomes [7, 8]. Underserved populations have consistently been shown to be at higher risk for late-stage diagnosis due to a combination of lower screening rates, missed appointments, and lack of timely referral to diagnostic evaluation and treatment [7–11]. Additionally, research has found that past mammography screening behavior is strongly correlated with current screening behavior, meaning that women who are off-schedule with screening are less likely to become adherent [12]. Appointment no-shows as they relate to the eventual completion of mammography screening have also been recently studied. Ontilo et al., 2013, found that women who missed a screening were more likely to be diagnosed at a later stage of cancer than women who attended [1]. In a 2012 study by Fayanju et al. of federally qualified health center (FQHC) patients in St. Louis, women who missed a screening appointment were significantly more likely to never receive definitive diagnosis or needed follow-up care [13]. A number of barriers prevent underserved women from obtaining timely screening, including patient-level socioeconomic differences like education, insurance, and income; differences in skills and qualifications of providers attending to different racial-ethnic groups; inadequacies in health care systems which provide care for the underserved; beliefs and misconceptions; and linguistic/communication barriers [8, 9, 14, 15]. A number of evidence-based intervention programs have been developed to address these barriers, yet disparities in breast cancer outcomes persist for underserved women. One reason for this may be the lack of uptake and use of evidence-based interventions in community and clinical settings that serve these women [16–20].

### The need for adoption and implementation support in clinics serving underserved populations

Dissemination and implementation processes for the uptake of evidence-based interventions (EBIs) remain poorly understood. The expertise of practitioners is often not used effectively, and implemented programs often do not ultimately reflect the needs of underserved communities within the specific context [17, 21, 22]. Particularly for interventions with minority communities, EBIs should be adopted and tailored at the community level by partnerships that include both researchers and practitioners, adding an additional level of complexity to the translation of these EBIs [23, 24]. Efforts to increase adoption and use of EBIs in community and clinical settings serving underserved women should target the safety net health care delivery system [25]. Within the safety net, primarily FQHCs and charity clinics provide comprehensive primary health care services for underserved communities regardless of ability to pay; this includes mammography screening [25, 26]. Additionally, the passage of the Affordable Care Act has significantly expanded the role of FQHCs who will be increasingly important in providing care for populations with a disproportionate burden of need [25]. Due to their client base, FQHCs are uniquely situated to reach and serve women in the most need for breast cancer screening [25]; however, FQHCs need assistance in planning and implementing EBIs [27, 28]. There is currently a lack of theoretically informed, well-documented, and evaluated implementation strategies for the translation of EBIs particularly within safety net clinical settings [4, 5]. Systematically designed implementation strategies are particularly important for the implementation of complex interventions—meaning interventions consisting of multiple behavioral, technological, and organizational components [3].

### Trial objectives

This study aims to address the research to practice gap and uses a theoretically based, strongly designed D&I strategy to support implementation of a breast cancer screening intervention aimed at promoting mammography adherence in underserved populations. Our patient navigation-based breast cancer screening intervention for the underserved is called the Peace of Mind Program (PMP). PMP is an EBI which was adapted from a National Cancer Institute Research tested intervention program and uses a tailored telephone counseling reminder call based on the Transtheoretical Model of Change to counsel patients through barriers to appointment attendance [20, 29–31]. PMP builds on our previous intervention protocol [30, 31] by adding intervention components to specifically support implementation within safety net clinics.

We hypothesize that the PMP intervention will improve mammography appointment adherence as compared to usual practice.

The specific objectives are:To assess implementation of the intervention at the clinics.To test the effectiveness of the PMP intervention in improving appointment adherence for screening mammograms.To test the effectiveness of the PMP intervention in reducing the time it takes for a patient with abnormal results to receive follow-up and navigation to a diagnostic appointment and subsequent treatment initiation.To assess the budget impact (cost savings) of the implementation of the PMP intervention from the perspective of the clinics.

## Methods

### Trial design

We will conduct a non-randomized stepped wedge design as shown in Fig. 1. Each clinic will serve as its own control and will not have access to the PMP prior to implementation. Clinics will implement the PMP for up to 47 weeks depending on their group assignment (see Fig. 1). The trial will follow the CONSORT extension for stepped wedge randomized trials reporting guidelines (see Additional file 1). Insert reference: [Hemming K, Girling A, Haines T, et al. Protocol: Consort extension to stepped wedge cluster randomised controlled trial. 2014].

**Fig. 1 Fig1:**
[figure not shown]
Stepped wedge trial design

### Participants and settings

The PMP trial will be conducted in FQHCs and charity clinics who are members of the Breast Health Collaborative of Texas (BHCT) network. BHCT is a state-wide network of over 700 clinics and individuals with a shared mission to improve access to breast health services for all women in Texas.

### Practice inclusion criteria

In order to participate, clinics must (1) be members of BHCT within the Houston service area, (2) have a designation as a FQHC by HRSA or be a charity clinic which provides free or reduced cost care to underserved populations in their service area, (3) be serving women between the ages of 40–64 who are at or below 200 % of the federal poverty level for a family of four and who lack health insurance, and (4) engage in provision of mammography screening services at least six times per year and (5) women at the clinic must be in need of mammography screening and be scheduled for an upcoming appointment. Patients must have completed a clinical breast exam prior to their screening appointment.

### Practice exclusion criteria

There are no practice exclusion criteria if serving patients within the Houston service area.

### Intervention components

The PMP intervention program consists of the following components: a financial incentive of $7500 to the clinic for participation; funding for screening mammograms for women with documented financial need; coordination of increased screening within each clinic (the research team has established partnerships with local mobile mammography providers to assist in increasing screening capacity); 8 h of state certified training for staff in the EBI’s reminder phone call protocol [20, 30, 31]; stakeholder review of program adaptation and implementation materials; stakeholder meetings to troubleshoot implementation issues as they arise and to develop and disseminate e-newsletters and reports which highlight success stories and re-inforce desired behaviors; technical support for implementation (implementation manuals, clinic manuals, stakeholder manuals); and assistance in data tracking and reporting and budget impact analysis.

### Sample size

Sample size for the stepped wedge design is calculated using the formula of Woertman et al. 2013 [32], which corrects a standard sample size calculation for two independent proportions as follows:$$ Nsw= Nu* DEsw $$

where *Nu* equals the uncorrected sample size estimate and *DEsw* is the design effect for the stepped wedge design.$$ DEsw=1+\rho \left(ktn+bn-1\right)*\frac{3\left(1-p\right)}{\left(1+p\right)\left(\frac{1}{2ktn}+bn-1\right)2t\left(k-\frac{1}{k}\right)} $$

where *ρ* equals the intraclass correlation, *k* equals the number of steps, *b* equals the number of baseline measurements, *t* equals the number of intervention measurements, and *n* equals cluster size. The uncorrected sample size for a difference in two independent proportions assuming a baseline no-show rate of 35 % reduced to 28 %, an α of 0.05 and a power of 0.9 equals 924 per group. The average no-show rate and expected reduction in no-shows are based on pilot studies [20, 30]. The intraclass correlation coefficient (ICC), *p*, for mammography screening interventions has been shown to range from 0.0009 to 0.22 in community-based trials with an average ICC of 0.06 based on recent systematic reviews [33, 34]. Estimated sample sizes based on these parameters are summarized in Table 1. Based on the average reported ICC, the required sample size is 388 women. The required number of clusters is calculated as *Nsw/n* resulting in an effective sample size requirement of seven clusters (clinics) [32]. In order to account for potential attrition estimated based on the investigator’s pilot study, the sample size will be increased by 20 % to 466 women across nine clinics.

**Table 1 Tab1:** Estimated sample sizes based on ICC reported values

*Nsw*	*Nu*	*DEsw*	*p* (ICC)
370	1848	0.20	0.006
388	1848	0.21	0.06
370	1848	0.20	0.1
333	1848	0.18	0.22

### Randomization and allocation

Clinic will be the unit of allocation in this study. Each clinic will be assigned a start date in groups of three (Fig. 1). Randomization of clinic start dates will not be done for practical reasons, including constraints in clinic operations (requirements for when they can or cannot start) and available screening dates (some clinics need additional time to reach the screening minimums required for study participation (*n* = 6)). The research team will assign a start date to each clinic based on these constraints.

### Blinding

Due to the nature of the intervention, it is not possible to blind the clinics or the research team in this study. However, outcome assessment is objective as we are using medical records to obtain screening outcomes. It is also not possible to blind the data analyst because the analysis is designed as a time series in which every clinic receives the intervention rather than a comparison between groups. The analysis will be pre-specified rather than blinded, and any analysis not pre-specified will be clearly delineated and considered hypothesis generating/exploratory rather than hypothesis testing/explanatory.

### Outcome measures

The primary outcome measure will be appointment adherence comparing the intervention period to the baseline period in each clinic. Appointment adherence will be considered using the following categories: no-show, not attended-called, late-screened, late-turned away, canceled/re-scheduled, and ineligible. A no-show will be considered a patient who makes no contact with the clinic prior to the appointment and does not attend on the day of mammography screening. A not attended-called is a patient who calls the clinic the day of the screening and asks to cancel or re-schedule (this may occur before or after their designated appointment time). Late-screened is a patient who arrives more than 30-min late for their appointment but is still seen by the mammography provided (e.g., worked in). Late-turned away is a patient who is more than 30-min late for their appointment and is turned away by the provider. A cancel or re-schedule is a patient who calls more than 24 h in advance to cancel or change their appointment date. An ineligible patient is a woman with symptoms who is ineligible to receive a screening mammogram and is turned away for a diagnostic evaluation or a woman who is turned away for incomplete paperwork. These categories are based on an assessment of the mammography providers’ and clinics’ behavior and the ways in which patient appointment outcomes are considered within a clinic system. Secondary measures will include patient referral to diagnostic (following screening) as a binary outcome and amount of time the referral took in days, patient referral to treatment as a binary outcome and the amount of time it took in days, and measures of implementation in each clinic based on the consolidated framework for implementation research (CFIR). A survey made up of scales assessing various CFIR constructs was developed by the Cancer Prevention and Control Research Network (CPCRN); we will use several scales from that survey in this study. These constructs will be measured at baseline (adoption), 8-week post-implementation, and following the end of the trial period (sustainment) [35–37]. Because randomization of start dates is not possible, we will control for potential confounders in the analysis of the data. Control variables may include time to intervention start date in each clinic, clinic size, staffing, and whether or not the clinic had a pre-existing patient navigation program for breast cancer screening, patient demographics, region served, and infrastructure characteristics (e.g., funding) (taken from the Health Resources and Services Administration Uniform Data System (UDS) reports for FQHCs and our economic survey).

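### The no-show rate that sizes the trial can fall through cancellations prompted by the PMP call, with no extra woman screened, and no contrast named in the plan would show it

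*Protocol article*

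**What the plan says.** All references are to the Protocol article.

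- **Intervention (Trial objectives).** PMP "uses a tailored telephone counseling reminder call based on the Transtheoretical Model of Change to counsel patients through barriers to appointment attendance".
- **Primary outcome (Outcome measures).** "The primary outcome measure will be appointment adherence comparing the intervention period to the baseline period in each clinic". Six categories follow. None of them is attendance on time.
- **No-show (Outcome measures).** "A no-show will be considered a patient who makes no contact with the clinic prior to the appointment and does not attend".
- **The two neighbouring categories of non-attendance (Outcome measures).** "A cancel or re-schedule is a patient who calls more than 24 h in advance to cancel or change their appointment date", and "A not attended-called is a patient who calls the clinic the day of the screening and asks to cancel or re-schedule". In both, the patient does the calling.
- **Sample size.** The calculation uses the no-show rate alone: "assuming a baseline no-show rate of 35 % reduced to 28 %, an α of 0.05 and a power of 0.9 equals 924 per group".
- **Statistical methods.** No-show and not attended-called may be pooled, as an option. An effect is expected, and will be evaluated, in five of the six categories. The missing one is canceled/re-scheduled, which is also outside the pooled definition.
- **Data collection.** Attendance is taken from the medical record.

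**The concern.** The event used for sizing depends on two things: whether the woman came, and whether she made contact beforehand. PMP acts on both. It may bring more women to the appointment, and it also gives a woman who will not come a conversation in which to say so. If she says so, she moves from no-show to another form of non-attendance and has not been screened.

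Two situations are not clearly placed. A woman who cancels during the navigator's call did not phone the clinic, yet she is not comfortably a patient without contact either. A woman who is reached, agrees to come and then stays away is naturally a no-show, but the text does not say so. Both arise mainly under PMP, because Budget impact analysis expects that many clinics may have no reminder mechanism in the control period.

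At stake is whether a fall in no-shows could be read as better appointment adherence when non-attenders had only been relabelled. Accurate abstraction does not remove this, because the abstractor must still apply an incomplete rule.

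**Working it through.** **1. The plan's own figure.** Inputs from Sample size: p1 = 0.35, p2 = 0.28, α = 0.05 (two-sided assumed), power 0.90.

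n per group = [1.960·√(2·p̄·(1−p̄)) + 1.282·√(p1(1−p1) + p2(1−p2))]² / (p1−p2)², with p̄ = 0.315

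= [1.960·√0.43155 + 1.282·√0.4291]² / 0.07², which rounds up to **924**, as stated. The power of that design comes back as 0.900.

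**2. Relabelling needed to produce the planned effect.** Let s be the share of would-be no-shows who, because of the call, move to another category of non-attendance. It is counted over and above what baseline reminder systems already cause. With no change in attendance:

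measured no-show rate = 0.35 × (1 − s)

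Setting this equal to 0.28 gives s = 0.07 / 0.35 = **20%**. Per 100 scheduled women, 35 silent no-shows become 28 no-shows and 7 cancellations. The other 65 are unchanged and the number screened is the same.

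**3. What that implies about the calls.** Write s = r × c, where r is the share of would-be no-shows reached and c is the share of those reached who cancel or re-schedule. Neither is in the documents, so r is assumed over a range and c = 0.20 / r:

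| r (assumed) | c needed for the full 7 points |
|---|---|
| 30% | 67% |
| 50% | 40% |
| 60% | 33% |
| 80% | 25% |
| 100% | 20% |

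**4. Smaller shifts.** Chance of a significant difference in no-shows with no gain in screening, at 924 per group:

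| s (assumed) | measured no-show rate | chance of significance |
|---|---|---|
| 5% | 33.25% | 12% |
| 10% | 31.5% | 36% |
| 15% | 29.75% | 67% |
| 20% | 28% | 90% |
| 30% | 24.5% | over 99% |

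These use the uncorrected calculation for independent samples, without the stepped wedge correction. They show how the risk scales and are not operating characteristics of the actual design.

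**5. Whether the planned analyses would reveal it.** Let a be the not attended-called rate, which is not given. If the 7 women move to canceled/re-scheduled, the pooled definition goes from 35 + a to 28 + a per 100. It falls by the same 7 points, so pooling does not close this route. The list of evaluated categories omits the one that would rise.

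**The case against.** **The patient is the one who makes contact.** This is the strongest point, and it limits the finding. The no-show sentence has the patient as its subject, and the neighbouring categories have her phoning. A reader might infer that answering the reminder call is itself the contact that takes a woman out of the no-show count, so that every non-attender who is reached is reclassified. The document does not support that. It nowhere says that an answered call counts, and on the natural reading a woman who answers and then does not come remains a no-show. The share of non-attenders reached is therefore not the share relabelled. What survives is cancelling or re-scheduling prompted by the call.

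**The no-show rate is not the sole primary outcome.** True. Adherence is reported by category, descriptive statistics cover all primary measures, and attendance is abstracted, so a careful reader of the tables might see the shift. Statistical methods also promises chi-square comparisons of sub-categories, but does not say which. The preceding list leaves canceled/re-scheduled out, and no contrast of screened with not screened is named.

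**Fewer no-shows is itself a goal.** Also true: the abstract's Discussion and Budget impact analysis both say so. A fall in no-shows with unchanged screening has some value, but it would not show that more women kept their appointments.

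**Coding of calls belongs in an abstraction manual.** A condensed article may leave that to the full protocol, and Data collection promises standardized procedures. This objection carries some weight for the unclassified cases. It does not answer the analysis section, which states its combined definition and its list and omits the relevant category from both.

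**Conclusion.** The concern holds in this form: the no-show measure on which the trial is sized can improve through call-prompted cancellations without more women being screened, and no contrast the article names is set up to detect that. Relabelling 20% of would-be no-shows, or 7 per 100 scheduled women, would reproduce the full planned effect. This is a threshold. Nothing in the documents shows that relabelling of that size will occur, and it matters only where it exceeds what control-period reminder systems already cause.

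The conclusion assumes that a cancellation made during the clinic's call would be coded outside no-show. If abstractors coded it as a no-show, that part of the shift would vanish, which is why the rule must be written down. A woman prompted by the call to ring back and cancel more than 24 h ahead fits the existing cancellation category exactly, so the route does not depend on the ambiguity alone.

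**What to change.** 1. **Outcome measures.** State that an answered clinic-placed call does not by itself change a woman's category. Classify a cancellation or re-scheduling by its timing, whoever placed the call. The timing bands should also meet: as worded, a cancellation less than 24 h ahead but not on the day falls in neither. Apply the same rule to baseline and PMP appointments. Baseline collection is already under way according to Trial status, so this should be settled now.
2. **Statistical methods.** Add canceled/re-scheduled to the categories evaluated. Analyse screened versus not screened among all scheduled women by the same GEE approach, and base any conclusion about improved appointment adherence on that contrast, not on the no-show rate alone.

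The first change alone is not enough. It removes the ambiguity, but a woman who cancels when called would still leave the no-show count unscreened. The second change closes that route with attendance data the trial already abstracts.

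The cost is two reworded definitions, one more model and a possibly smaller measured effect, because a woman who re-schedules counts as not screened at her original appointment.

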
### Data collection

Data collection protocols will be standardized across all clinics. In clinics with the capability to collect and report data from their electronic health record (EHR), the research team will seek to adapt the existing system for data collection. In clinics where the EHR is not easily modified or one is not available, data collection will be supported via the use of a customized Redcap database. The database will have a front-facing data entry interface which is user friendly and supports accurate data collection for statistical analysis. The patient navigator (or implementer) in each clinic will be responsible for tracking upcoming patient mammography appointments, reminder phone call attempts, patient consent for the trial, and the EBI screening questions and barriers counseled during the phone call. Appointment attendance, referral to diagnostic mammography, and treatment data will be abstracted from medical records in each clinic. For the budget impact analysis, two surveys will be used to assess the FQHC/clinic resource utilization before and after the implementation of the intervention. We are also collecting patient resource utilization data to understand what parts of patient costs are being subsidized by the FQHCs/clinics and to also ensure availability of cost information from patient perspective in case an economic evaluation from societal perspective is deemed important.

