### Statistical methods

Descriptive statistics will be calculated for all primary and secondary measures. Following descriptive analysis, regression modeling will be used to evaluate outcomes while allowing for control of potential confounders (e.g., time, clinic size, staffing, and whether or not the clinic had a pre-existing patient navigation program for breast cancer screening). Due to the correlated nature of the data and repeated observations taken on each clinic, generalized estimating equations (GEE) will be used to model outcomes while allowing us to control for potential confounders [38, 39]. GEE is used to estimate the parameters from a generalized linear model when there is possible correlation between outcomes [38, 39]. GEE is a population averaged model that estimates the average response from a change in a covariate over the population rather than individual [38, 39]. GEE model estimates are less sensitive than generalized linear mixed models to the specification of the variance structure in the data making them a flexible choice [38, 39]. Data on appointment adherence will be analyzed using various sub-groups to evaluate the intervention effect. For example, no-shows and not attended-called may be combined to consider a more stringent definition of a no-show. They will also be analyzed separately. We expect the intervention to have an effect on the no-shows, not attended-called, late-screened, late-turned away and ineligible categories and will evaluate that effect separately. Sub-categories will be compared using chi-square tests to determine differences in outcomes between groups (control and intervention). Data from the CFIR survey will be analyzed using descriptive statistics and in the regression models to evaluate which constructs are related to implementation outcomes. Data analysis will be conducted in Stata (Stata Corp., College Station, TX).

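### The *ineligible* outcome category pools symptomatic women sent for diagnostic work-up with women sent home over paperwork, so a change in its rate cannot be read as benefit or harm

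*Protocol article*

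**What the plan says.** Outcome measures names appointment adherence, intervention period against baseline period in each clinic, as the primary outcome. It lists six categories: "no-show, not attended-called, late-screened, late-turned away, canceled/re-scheduled, and ineligible". The last is given two alternative routes of entry. It applies to a symptomatic patient, described as "ineligible to receive a screening mammogram and is turned away for a diagnostic evaluation or a woman who is turned away for incomplete paperwork". No sub-code by reason is given.

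Statistical methods lists the categories on which an intervention effect is expected, ending with "late-screened, late-turned away and ineligible categories and will evaluate that effect separately". The same section plans chi-square comparisons of the sub-categories between control and intervention. It states no expected direction for *ineligible* and no split by reason.

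Two other statements bear on the category. Practice inclusion criteria says "Patients must have completed a clinical breast exam prior to their screening appointment". Blinding says that any analysis not laid down beforehand will be treated as exploratory.

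**The concern.** A single outcome category should hold events that point the same way. These two do not. A woman sent home over paperwork had a usable appointment and left without a screen, which is the kind of failure a navigation programme could reduce. A symptomatic woman sent on for diagnostic evaluation came to her appointment and, on the protocol's own definition, did not qualify for a screening mammogram. Fewer of the first is an improvement. Fewer of the second is not obviously good or bad.

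The plan nevertheless expects an effect on the pooled category and tests it separately. A significant result could be reported as a programme effect on adherence when it reflects only a change in how many symptomatic women reached the screening visit. A null result could conceal two real movements that cancel. Because the article makes unplanned analyses exploratory, a split made after the data are in would lose its standing under the trial's own rule.

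**Working it through.** **1. The plan's own figure.** The article gives no rate for *ineligible* or for either reason, so there is nothing on this point to reproduce. The nearest figure is the uncorrected sample size under Sample size: no-show 35% against 28%, α 0.05, power 0.9. With a two-sided test, pooled variance under the null and mean proportion 0.315:

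n = [1.960 × √(2 × 0.315 × 0.685) + 1.2816 × √(0.35 × 0.65 + 0.28 × 0.72)]² / 0.07² = (1.2875 + 0.8395)² / 0.0049 ≈ 923.3, rounded up to **924 per group**, as stated.

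That calculation uses no-shows only. Nothing below changes it.

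**2. Why the pooled rate is not interpretable.** Let S be the proportion of scheduled appointments ending in a symptomatic turn-away, P the proportion ending in a paperwork turn-away, and I = S + P. Only I is analysed, so the change in I is one equation in two unknowns. Assume S = P = 3% at baseline (illustrative, not from the article) and suppose I is seen to fall from 6% to 4.5%:

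| Cause | S | P | I |
|---|---|---|---|
| Symptomatic turn-aways halve, paperwork unchanged | 3% → 1.5% | 3% → 3% | 6% → 4.5% |
| Paperwork halves, symptomatic unchanged | 3% → 3% | 3% → 1.5% | 6% → 4.5% |

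The two causes give the same pooled result with opposite conclusions about paperwork. Even with the baseline split known, an observed 4.5% allows P to be anything from 0% to 4.5%, a change of −3.0 to +1.5 points.

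**3. Allowing for a change in attendance.** Take arrivals as 1 minus the planned no-show rate, 65% at baseline and 72% under the intervention. This is a simplification, because *not attended-called* and *canceled/re-scheduled* are non-arrivals too. Each component is arrivals × its assumed share of arrivals, with shares of 2% to 5%:

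| Share symptomatic | Share paperwork | Change in S | Change in P | Pooled I |
|---|---|---|---|---|
| 5% → 5% | 5% → 2.5% | 3.25% → 3.60% (+0.35) | 3.25% → 1.80% (−1.45) | 6.5% → 5.4% |
| 5% → 2.5% | 5% → 5% | 3.25% → 1.80% (−1.45) | 3.25% → 3.60% (+0.35) | 6.5% → 5.4% |
| 2% → 2% | 5% → 2.5% | 1.30% → 1.44% (+0.14) | 3.25% → 1.80% (−1.45) | 4.55% → 3.24% |
| 5% → 5% | 2% → 1% | 3.25% → 3.60% (+0.35) | 1.30% → 0.72% (−0.58) | 4.55% → 4.32% |
| 5% → 2.5% | 5% → 2.5% | 3.25% → 1.80% (−1.45) | 3.25% → 1.80% (−1.45) | 6.5% → 3.6% |

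Rows 1 and 2 give an identical pooled fall, with paperwork better by 1.45 points in one and worse by 0.35 in the other. Row 5 shows both components falling together. S falls only if its share of arrivals drops by more than 1 − 65/72 = 9.7%. Opposite movement is therefore possible but not inevitable.

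**4. What a split does not cure.** Suppose S = P = 3% of appointments, paperwork failures per arrival fall by 10%, and arrivals rise from 65% to 72%. Then I goes from 6.0% to (3 + 2.7) × 72/65 = 6.3%. Paperwork alone goes from 3.00% to 2.7 × 72/65 = 2.99%. The gain is invisible with or without the split, because it is rising attendance that offsets it.

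**The case against.** The strongest reply is that this is one category of unknown size, separate from no-show. The required breast exam beforehand may leave few symptomatic arrivals. Attendance is abstracted from medical records, so the reason could be recovered. A data dictionary or analysis plan not shown here may already hold sub-codes. Most of this stands as a limit on weight. It does not remove the point, because the article itself defines the pooled category and says an effect on it will be evaluated. That is a stated choice, not a detail left out.

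A reader might be tempted by stronger readings. The article does not support them:

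- *Symptomatic women are lost from the diagnostic-referral endpoint.* The article says "Secondary measures will include patient referral to diagnostic (following screening) as a binary outcome", and the matching item under Trial objectives concerns patients with abnormal results. A woman who was not screened has no screening result, so she lies outside the scope of that endpoint and is not lost from it.
- *Symptomatic women count against adherence, or the denominators differ between periods.* Nowhere is *ineligible* said to count as non-adherence, and such a woman cannot be a no-show under the article's definition.
- *The reminder call redirects symptomatic women in advance.* Data collection mentions "the EBI screening questions and barriers counseled during the phone call", but the content of the questions is not given. This is one possible route for a change in S, not an established one.
- *Pooling necessarily yields opposing effects, or hides a paperwork gain when attendance rises.* Both components could fall together (step 3), and in the case in step 4 the split does not bring the gain to light.

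**Conclusion.** The point holds in a limited form. The article fixes one category for two events of different meaning and plans to evaluate an intervention effect on it without a stated direction. Followed as written, the result for that category cannot be read as benefit or harm. The size cannot be fixed from the article. Under the assumed rates, the same pooled fall of 1.5 points (step 2) or 1.1 points (step 3) is compatible with better, unchanged or worse paperwork performance. The conclusion itself does not depend on those rates. It rests only on both reasons occurring, and on reading a turn-away as a woman who came to the appointment. It concerns the interpretation of one category and leaves the no-show comparison and the sample size as they are.

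**What to change.** Under Outcome measures, replace *ineligible* by two codes: (a) symptomatic, sent for diagnostic evaluation; (b) sent home because paperwork was incomplete. Apply the same coding rules in the baseline and intervention periods. Under Statistical methods, analyse (b) as an attended-but-not-screened outcome that the intervention is expected to reduce. Report (a) descriptively by period and do not test it as an intervention effect. Show the number attending in each period beside (b), since its rate per scheduled appointment also moves with attendance.

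Keep every scheduled woman in the main adherence denominator. Do not exclude women whose symptoms come to light only at the reminder call. Trial design gives clinics no access to the programme before implementation, so there is no such call at baseline, and the exclusion would act in one period only.

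The cost is one extra code. The reason must already be known to assign the present category. Trial status says baseline collection is under way, so some baseline records may need re-abstraction.
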